### Objectives and hypotheses

The primary objective of this study is to investigate whether a twelve-week cognitively challenging PA intervention in children and adolescents with cancer has a positive effect on their EFs.

Secondary objectives are to investigate whether the twelve-week cognitively challenging PA program has a positive effect on cardiovascular health, motor abilities, body composition, psychosocial functioning, HrQoL and fatigue. Additionally, feasibility, safety, and adverse events of our PA program will be assessed. A PA counseling in maintenance therapy or aftercare will be offered to all participants, and its feasibility will be explored using qualitative interviews.

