### Statistical analysis

#### Sample size calculation

Two sample size calculations were performed for the primary outcomes: one encompassing both inhibition and cognitive flexibility and another for working memory. The calculation for the former is presented below, as it yielded the larger sample size needed, which was therefore selected for the study.

The sample size calculation was done using G*Power 3: Repeated measures ANOVA with four measurement points and two groups (within-between interaction), a statistical power of 80%, a small effect size (Cohen’s *f* = 0.105) [54], an α = 0.05 and a retest correlation of 0.8. This results in a minimum sample size of *N* = 52 in total, i.e. 26 subjects per group. To compensate for losses and drop-outs, we set the minimal sample size to *N* = 70.

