#### Statistical analysis plan

Study sample characteristics will be shown separately as mean values (x̄) with its standard deviation (±) for each group regarding continuous variables. For categorical variables percentages and absolute numbers will be used. Normal distribution will be analyzed by the Shapiro-Wilk test and graphical verification of the Gaussian distribution. For all analyses, the significance level will be set at *p* < 0.05 and effect sizes will be provided.

*Preliminary analyses* will be performed to ensure that characteristics of the study participants (e.g., age, sex, diagnosis, weight, height) are comparable between the IG and CG using independent *t-*tests (continuous variables) or chi-squared tests (categorical variables). For feasibility analysis, descriptive statistics will be used.

The *main analyses* for the primary and secondary outcomes are repeated measures ANOVAs (for normal distributed data) and the Friedman test (for non-normally distributed data), where the “between-group” factor describes the IG vs. CG and the “within-group” factor is “timepoint” (T0, T1, T2, T3). If linear mixed models converge (despite small sample size), they will be used instead of repeated measures ANOVAs. These models will be specified to adjust for potential baseline imbalances [109]. They include the main effect of time and the group-time interaction. As the period between the data collection waves most probably will not be equal for all participants, as a time variable, the individual time interval in days will be used to increase the precision with which a child’s growth trajectory is measured. For each dependent variable, the optimal model will be determined using likelihood-ratio tests for nested models and Akaike information criterion for non-nested models. For these comparisons a random intercept model will be compared to a fixed effects model and a model including random intercepts and fixed effects. The model with the best fit will subsequently be chosen.

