For *supplementary analyses*, we will perform the same analyses for different age groups (6–11.99 and 12–17.99 years), cancer types (e.g. leukemia, brain tumors) and chemotherapy severity levels with sufficient sample size (*n* > 20). In addition, baseline performance will be correlated with gain scores using Pearson correlations (for normally distributed data) or Spearman correlations (for non-normally distributed data) for outcomes that show significant group × time interactions. To explore associated changes in certain variables, changes in motor abilities will be correlated with changes in core EFs and psychosocial functioning.

Additionally, for the intention-to-treat (ITT) analyses, we will perform two per protocol analyses. In the first per protocol analyses, only participants will be included, who did at least 80% of the PA sessions, in the second per protocol analyses participants will be included, if they completed 60% of training sessions. For all statistical analyses, the statistical program R and SPSS will be used.

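### The exploratory correlation of motor change with EF change names no adjustment for group; pooled over both arms, it would partly restate the two intervention effects the trial hypothesises.

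*Protocol article*

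**What the plan says.** The protocol article, under Statistical analysis plan, lists several supplementary analyses. One is introduced with "To explore associated changes in certain variables" and states that "changes in motor abilities will be correlated with changes in core EFs and psychosocial functioning". The sentence gives no estimator. The one before it, on a neighbouring question, says that "baseline performance will be correlated with gain scores using Pearson correlations (for normally distributed data) or Spearman correlations (for non-normally distributed data". Neither sentence mentions group, a partial correlation or a split by arm. By contrast, the main analyses in the same section spell out a between-group factor and an adjustment for baseline imbalance.

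The section also says "For all analyses, the significance level will be set at *p* < 0.05", so this correlation would be tested as well as described.

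Under Objectives and hypotheses, the primary question is whether the "cognitively challenging PA intervention in children and adolescents with cancer has a positive effect on their EFs". The secondary question is whether the programme "has a positive effect on cardiovascular health, motor abilities, body composition, psychosocial functioning, HrQoL and fatigue". Both sides of the planned correlation are therefore outcomes that the intervention is expected to move.

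**The concern.** When an intervention raises two outcomes, children in the intervention arm tend to sit high on both change scores and control children low on both. Pooling the arms turns these two mean differences into a positive correlation, even if, among children treated alike, those who gain more in motor ability gain no more in EF. The result would be read as showing that motor gains go with cognitive gains in the same child, although it might only repeat the two group comparisons already reported. The distortion is greatest when the programme works on both outcomes, which is when the analysis would attract most attention.

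**Working it through.** **Inputs from the protocol article.** Sample size calculation: four time points, two groups, f = 0.105, retest correlation 0.8, α = 0.05, power 80%, N = 52 raised to 70. Participants: 35 per arm.

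**Assumptions, not in the document.** The effect on motor change equals that on EF change unless varied below, and the within-arm correlation of the changes is zero.

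**1. The plan's own figure.** For the within-between interaction, λ = f²·N·m/(1 − ρ), with degrees of freedom 3 and 3(N − 2). At N = 52, λ = 0.011025 × 52 × 4/0.2 = 11.47, and power is 0.811. At N = 50, power is 0.793. The smallest even N is 52, so the stated figure reproduces.

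**2. The EF effect implied on the change scale.** Let the arm difference follow a pattern over T0 to T3 with peak D. Then f = D × SD(pattern)/2, so D = 0.21/SD(pattern). The SD of a change score is √(2 × (1 − 0.8)) = 0.632, and d = D/0.632.

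| Pattern of arm difference | D | d | Pooled r if both outcomes have this d |
|---|---|---|---|
| 0, 1, 1, 1 | 0.485 | 0.77 | 0.128 |
| 0, 0.5, 1, 1 | 0.507 | 0.80 | 0.138 |
| 0, 1/3, 2/3, 1 | 0.563 | 0.89 | 0.166 |
| 0, 0.5, 1, 0.5 | 0.594 | 0.94 | 0.181 |

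Here d is for change from T0 to the peak difference. The plan does not say which interval the change covers, and another interval can carry a smaller d. For example, the linear pattern gives 2/3 × 0.89 = 0.59 at T2, and then r = 0.081.

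**3. The induced correlation.** With equal arms and zero within-arm correlation, pooled r = (d₁d₂/4)/√[(1 + d₁²/4)(1 + d₂²/4)]. For d₁ = d₂ = 0.8 this is 0.16/1.16 = 0.138.

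**4. How often the 5% test rejects** (simulation, 20,000 replicates).

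| d for EF | d for motor | Pooled r | N = 52 | N = 70 |
|---|---|---|---|---|
| 0.89 | 0.89 | 0.165 | 22.1% | 27.8% |
| 0.8 | 0.8 | 0.138 | 16.3% | 20.8% |
| 0.8 | 0.5 | 0.090 | 9.6% | 11.3% |
| 0.5 | 0.5 | 0.059 | 7.0% | 8.0% |
| 0.8 | 0.2 | 0.037 | 5.8% | 6.0% |
| 0.8 | 0 | 0 | 4.8% | 5.2% |

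For the two outer patterns in step 2, the Fisher z approximation with standard error 1/√(N − 3) gives the following. At N = 70, r = 0.128 has z-ratio 0.129 × 8.19 = 1.05 and rejects in about 18%; r = 0.181 has z-ratio 0.183 × 8.19 = 1.50 and rejects in about 32%. At N = 52 the figures are about 15% and 25%.

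**5. After the fix.** With arm means removed, mean r is about 0.00 and the rejection rate is 4.6% to 5.2% in every scenario at both sample sizes.

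**The case against.** **Pooling is not stated.** The article does not say that the arms will be combined, and a full analysis plan may settle it. This stands in part. A single correlation with no group term is the plain reading, but a reader who infers that the protocol has decided to ignore group goes further than the text.

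**The pooled correlation is a legitimate quantity.** In the scenarios above, the correlation across all children really is 0.13 to 0.18, so rejecting zero is no error for that marginal association. This is correct. Rejection misleads only if the result is taken as a link between the changes among children treated alike. The plan does not say which is meant, and showing both versions removes the ambiguity.

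**The effect is small and partly assumed.** This also stands. No motor effect size is given, an r of 0.138 is under 2% of shared variance (0.138² = 0.019), and effect sizes are to be reported. With a weak motor effect nothing is left to correct.

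**Two stronger readings are not supported.** A reader might infer that the correlation is central to the study's rationale. The Background rests on cognitive stimulation, and no listed objective says that motor gains track EF gains. A reader might also infer that age creates the same artefact, since both abilities develop between 6 and 17 years. That concerns levels, whereas the analysis uses changes. Age would matter only if the rate of change on both outcomes varied with it, and the document gives no figure for that.

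**Conclusion.** The point holds as a minor improvement to an exploratory analysis. The article names no handling of group for a correlation between outcomes that it expects the intervention to move together. If the arms are pooled, the EF effect matches the planning value at the time point used, the motor effect is equal and the within-arm correlation is zero, then r is about 0.13 to 0.18. The nominal 5% test then rejects roughly four to six times as often as 5% at N = 70 for the two middle time patterns, and somewhat less or more for the outer ones. With a small effect on either outcome the artefact disappears. The same mechanism applies to motor and psychosocial change, which was not quantified. No primary or secondary conclusion depends on this analysis.

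**What to change.** Add one sentence to the supplementary analyses. It should say that the association between changes will be estimated adjusted for group, by partial correlation or by regressing EF (or psychosocial) change on motor change with a group term, and that correlations within each arm will be shown alongside. The pooled value can still be reported if it is labelled as including the intervention effect. Adjusting for age and baseline value is optional.

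This needs no new data. It costs one degree of freedom for group and a few in all if the optional covariates are added. The within-arm correlations, at about 26 to 35 children each, will be imprecise and serve as description. If a within-arm analysis was already intended, the sentence puts it on record before the data are seen.

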#### Missing data

Dropouts will be documented with detailed information regarding their causes. Dropouts will not be replaced to comply with the ITT principle. Depending on the amount of missing data, it will be handled using single (< 5% missing data) or multiple imputation (≥ 5% missing data) methods or in the case of linear mixed models with maximum likelihood estimation.

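### Outside the mixed model, outcomes with under 5% missing are singly imputed; with prediction-type imputation the 5% group-by-time ANOVA test then runs at about 5–8% (minor)

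*Protocol article*

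**What the plan says.** The Missing data section sets the method by a count: "it will be handled using single (< 5% missing data) or multiple imputation", the latter from 5% missing upwards. The sentence goes on: "or in the case of linear mixed models with maximum likelihood estimation".

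The Statistical analysis plan section names the main analyses as "repeated measures ANOVAs (for normal distributed data) and the Friedman test (for non-normally distributed data"), where "the “within-group” factor is “timepoint” (T0, T1, T2, T3"). Mixed models take precedence under a condition: "If linear mixed models converge (despite small sample size), they will be used instead of repeated measures ANOVAs". The Friedman route is not said to be replaced. On the threshold, the section says: "For all analyses, the significance level will be set at *p* < 0.05".

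The article attaches no variance correction to the single-imputation branch. It also does not say which single-imputation method is meant or what the 5% is counted over. A fuller protocol or analysis plan may settle those two details; the rule itself is stated here.

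**The concern.** A singly imputed value enters the analysis with the same weight as a measured one. If it is a prediction from the arm or from a model, it brings no new information about the arm difference, yet the test counts it as a full observation. Without added noise it also shrinks the residual variance. The standard error is then too small and the test rejects too often.

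The limit of under 5% does not fix how many values may be treated this way. Counted per visit it allows 3 of 70 children (4.3%; 4 of 70 is 5.7%). Counted over an outcome it allows 13 of 280 values (4.6%; 14 of 280 is exactly 5%). Those 13 could all sit at one visit in one arm, where they would be 13/35 = 37% of that cell. Any outcome that takes this branch could therefore be tested at a level above the one declared.

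**Working it through.** **Inputs from the article.** Two groups of 35, four time points, α = 0.05, Cohen's f = 0.105, retest correlation 0.8. The design test is given as "Repeated measures ANOVA with four measurement points and two groups (within-between interaction), a statistical power of 80"%.

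**The plan's own figure.** For the within-between interaction, λ = f²·N·m/(1 − ρ), with df₁ = 3 and df₂ = 3(N − 2). At N = 52, λ = 0.011025 × 52 × 4 / 0.2 = 11.47, df₂ = 150 and power is 0.811. At N = 50, λ = 11.03 and power is 0.793. The stated minimum of 52 is reproduced. Going from 52 to 70 allows for 1 − 52/70 = 25.7% losses.

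**Hand check of the mechanism.** Take one visit, imputation by arm mean, and a fraction p of the tested values missing. The mean rests on (1 − p)n values, so its true variance is σ²/[(1 − p)n]. The filled-in data give about (1 − p)σ²/n. The reported standard error is therefore about (1 − p) times the true one, and the type I error is about 2[1 − Φ(1.96(1 − p))]. For p = 0.05 this is 2[1 − Φ(1.862)] = 6.3%. To reach 7%, about 7.6% of the tested values must be missing; to reach 11%, about 18%.

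**Simulation of the planned test.** Null trials with N = 70 and compound symmetry were simulated, values were deleted completely at random and imputed once, and the 3-df group-by-time ANOVA test was applied at 0.05. The correlation was 0.8, with 0.5 as a variation. The pattern of missingness and the imputation methods are assumptions, because the article gives neither. With 8,000 to 80,000 replicates per scenario, the Monte Carlo standard error at 5% is at most √(0.05 × 0.95/8000) = 0.24 percentage points. The ranges span methods and runs.

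| Missing data | Arm mean, regression or stochastic regression |
|---|---|
| None (full data) | 4.6–5.3% |
| 3 of 70 children, one follow-up visit or all of them | 5.0–6.7% |
| 13 of 280 values scattered over T1–T3 | 6.7–8.2% |
| 13 values all at one visit, either arm | 7.1–7.9% |
| 13 values all at one visit, one arm | 8.1–9.3% |

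- With fewer scattered gaps, arm-mean and regression imputation gave 5.3% (1% missing), 5.6–5.9% (2%), 6.0–6.4% (3%) and 6.5–7.1% (4%).
- With 52 children and scattered gaps, the rate was 6.7–7.7%.
- Last value carried forward stayed at 4.9–5.1%. The grand mean stayed near 5%, with 5.8% in the one-arm, one-visit pattern.
- A REML mixed model on the available values, with just under 5% of values missing and no imputation, rejected in 4.5% of 1,500 trials (Monte Carlo standard error 0.6 percentage points), which is nominal.

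The Friedman route was not simulated. That test has no between-group term, so these rates do not describe it.

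**The case against.** The strongest reply is that the branch is narrow. Mixed models use maximum likelihood and replace the ANOVA whenever they converge. A random-intercept model with visit and group-by-visit terms converged in every one of 300 null datasets per setting (N = 70, correlation 0.8 or 0.5, 13 or 70 of 280 values missing). The sample size allows for about 26% losses and the Discussion expects missing data, so most follow-up outcomes would pass 5% and go to multiple imputation anyway. The method is also unnamed, and last value carried forward would not inflate the test. All of this stands, and it is why the point is minor. It does not make the branch sound. Other models listed in the plan may fail to converge, the subgroup analyses repeat the same steps on samples that may only just exceed 20, and last value carried forward can bias estimates.

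A reader might infer more: that every outcome with under 5% missing is singly imputed, and that the 5% test then runs at up to 11%. The documents do not support this. The same sentence exempts mixed models. Rates of 10–11% arise only in single-visit comparisons between arms, with all the gaps at that visit, and the article does not plan such a test: it uses gain and change scores only in correlations. For the planned interaction test the worst case was 9.3%.

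**Conclusion.** The concern holds in a limited form. In the ANOVA fallback and any other imputed analysis, single imputation below 5% missing understates standard errors if the imputed values are predictions from the arm mean or a regression. Adding random noise to a single regression prediction does not cure it.

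The size depends on how the 5% is counted. The nominal 5% group-by-time test runs at about 5–6% (6.7% at most) if it is counted per visit or per child, and about 7–8% if it is counted over all 280 values and the gaps are scattered. It reaches about 9% only if all gaps fall at one visit in one arm. These figures assume normal data, compound symmetry and values missing completely at random. Analyses by mixed model with maximum likelihood are unaffected. Severity is minor: the branch will seldom be used, but it is a stated rule that can give error bars that are too narrow and has no advantage over the multiple imputation already planned.

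**What to change.** Delete the single-imputation branch. State that any outcome not analysed by the mixed model is handled by multiple imputation whatever the amount missing. The imputation model should include group, visit and the outcome's values at the other visits, and estimates should be pooled by Rubin's rules. For any rank test, name the method by which the test statistic is pooled, since Rubin's rules for estimates do not cover it directly. The threshold of 5% and the question of its denominator then fall away.

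The cost is a sentence or two in the plan and slightly more analysis work. Multiple imputation is already foreseen for 5% or more missing.

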#### Data management

RedCap will be used for data storage hosted by the Clinical Trials Unit Bern. For each participant, an electronic case report form is maintained within RedCap. This means that all digital data will be stored there. Data initially recorded in paper format (storage in locked files) will be digitalized and transferred to RedCap. Subject confidentiality will be ensured by utilizing subject identification coding numbers.

#### Data monitoring

Data monitoring will be conducted regularly, including routine verification of data quality performed by the principal investigator or his designees. All severe adverse events will be documented and reported immediately to the principal investigator. Furthermore, the Swiss Ethics Committee reserves the right to carry out audits and inspections at any time with full access to the data.

## Discussion

This study protocol outlines the design and methodology to investigate the cognitive and physical effects of cognitively challenging PA in pediatric cancer patients. Research suggests, that engaging in cognitively challenging PA in a playful setting has a beneficial effect on cognition, particularly in healthy children [53, 110]. This is because such exercises activate specific brain networks thereby enhancing EFs [36, 111]. Therefore, this approach could possibly serve as a preventive strategy for cognitive and physical impairments in children and adolescents undergoing cancer treatment [5, 9, 45, 49]. The intervention is designed based on the “S2k Guideline: Promotion of Exercise and Exercise Therapy in Pediatric Oncology” and the international Pediatric Oncology Exercise Guidelines [1, 50]. Additionally, it incorporates evidence from previous research studies and practical insights gained during cognitive training and PA interventions to optimize its effectiveness [51–54]. Finally, combining PA and cognitive tasks simultaneously can improve cognitive performance and encourages the children to remain active [36, 37, 112].

The main strength of this study is its uniquely designed approach for children and adolescents with cancer. Since the PA intervention offers varying levels of difficulty for the physical and cognitive tasks it ensures inclusivity. Through supervision, and knowledge of the underlying disease, the physical and cognitive intensity levels can be adjusted individually to avoid overload and to provide optimally cognitively challenging PA. Furthermore, integrating supervised PA during acute cancer care with structured PA counseling for the post-acute phase facilitates the promotion of sustained long-term effects. The study addresses a difficult-to-reach patient population, as participants alternate between inpatient and outpatient visits. We mitigate this and so reduce dropout by offering online exercise sessions, reaching patients at home.

A key limitation of the study is the heterogeneity of the patient population with different cancer types, age, treatment methods and duration. Moreover, randomization is not feasible, as it is ethically unjustifiable to withhold the PA intervention from eligible children and adolescents in the same clinic. Furthermore, the patients’ state of health may lead to low adherence to PA and missing data. Additionally, blinding of the study staff is not possible due to the study design of the intervention group assignments.

